## Discussion

This study is adequately powered to test the hypothesis that an individualized PEEP titrated by Cstat ventilation strategy can benefit obese patients in terms of perioperative oxygenation index, proportion of collapsed lung area, change in inflammatory factors, and incidence of PCCs, compared with an ordinary PEEP ventilation strategy.

PPCs related to general anesthesia and mechanical ventilation have attached more and more attention. Evidence suggests that lung-protective ventilation strategies are found to be effect on reducing the incidence of PPCs. Young and other six experts [4] reached an international expert consensus which included recommendations such as low *V*_*T*_, PEEP, and ARM. And in this consensus, an individualized PEEP was strongly emphasized. But how to set an iPEEP level, especially for special obese patients, is still uncertain.

Obesity has become a global health problem. During 2013–2016, 38.9% of US adults had obesity and 7.6% had severe obesity [19]. In obese patients, the accumulation of fat in the chest and abdomen limits thoracic activities. In supine position, the abdominal organs push up the diaphragm, further limiting the lung-thoracic compliance. In addition, the alveolar ventilation volume is decreased and FRC is reduced in these patients. Pulmonary infection and atelectasis are easy to occur during mechanical ventilation under general anesthesia [8–12]. Pneumoperitoneum pressure during laparoscopic surgery further reduces chest wall and lung compliance in obese patients and significantly increases the probability of intraoperative hypoxia and PPCs. The incidence of atelectasis after upper abdominal surgery in obese patients is as high as 45% and can last several weeks after surgery. For patients undergoing general anesthesia with mechanical ventilation, about 75% of patients develop a state of local alveolar non-ventilation during surgery. Local atelectasis leads to ventilation/blood flow imbalance and intrapulmonary shunt and even induce hypoxemia, which is more pronounced in obese patients [20–23]. Compared with zero end-expiratory pressure (ZEEP), PEEP can improve end-expiratory long volume (EELV), increase oxygenation, and improve respiratory system compliance (C_RS_), dependent lung ventilation, and post-operative lung function [24]. However Pirrone et al [25] found that PEEP commonly used by clinicians was insufficient for mechanical ventilation in morbidly obese patients.

Low tidal volume is one of the lung-protective ventilation strategies. Although low tidal volume can significantly reduce the incidence of ventilator-associated lung injury and reduce mortality, low tidal volume ventilation is not conducive to recruitment of collapsed alveoli in obese patients [13, 26]. Alveolar recruitment maneuvers (ARMs) are beneficial in reopening collapsed alveoli. After recruitment of collapsed alveoli, appropriate PEEP needs to be selected to maintain and prevent alveolar collapse again. However, too high PEEP will lead to alveolar overdistension and aggravate lung injury, while too low PEEP will lead to alveolar collapse again. Therefore, finding the optimal PEEP level is a problem that has been continuously explored in clinical practice.

The earliest goal of PEEP was to correct hypoxia, and many physiological studies have shown that PEEP levels of at least 5 cmH_2_O are necessary. Most scholars recommend that obese patients should be given 10 cmH_2_O PEEP, but the correction of hypoxia is not the ultimate goal. A reasonable PEEP should improve hypoxia, promote recruitment of collapsed alveoli, and prevent overdistension of alveoli [27]. Relevant studies have shown that individualized PEEP strategy compared with ordinary PEEP ventilation strategy can counteract the reduction of end-expiratory volume, improve respiratory mechanics and reduce intrapulmonary shunt, enhance oxygenation capacity, and improve the patient’s intraoperative ventilation [6].

How to set an ideal and individualized PEEP for obese patients in laparoscopic surgery is a difficult problem. The setting of PEEP shall be individualized to eliminate the effect of chest wall and abdominal high pressure on actual transpulmonary pressure and effectively improve the heterogeneity of gas distribution in the lungs. In this study, by gradually increasing and maintaining PEEP at 5 to 20 cmH_2_O, increasing the PEEP step by step according to the gradient until the calculated Cstat shows a decreasing trend; their previous PEEP (PEEP corresponding to the highest Cstat) will be set as the optimal iPEEP for this obese patient. According to our clinical work habits and other research recommendations [10, 11, 14], we set 5 cmH_2_O PEEP value as our control group PEEP, so as to verify the effectiveness of Cstat titration iPEEP.

Chest CT can accurately evaluate the size of lung recruitment and PEEP-induced lung recruitment. It calculates the tissue volume and gas volume in the lung tissue region by measuring the CT value. However, it is difficult to perform clinically and has the disadvantages of ionizing radiation. Electrical impedance tomography (EIT) can provide the gas distribution characteristics and mechanical characteristics of local lung tissues of patients by monitoring the change of intrathoracic impedance from lung ventilation [24, 28]. Compared with gold standard CT, EIT has the advantages of non-invasive, bedside, real-time, no radiation, etc. It has gradually become a research hotspot of clinical application and lung-protective ventilation in obese patients. EIT allows visual comparison and evaluation of regional lung tissue collapse and recruitment, as well as determination of lung volume and correlation with global respiratory mechanics. The application of EIT makes it possible to detect the patient’s lung collapse at the bedside.

In this study, ventilator-driven alveolar lung recruitment will be performed using the incremental PEEP method with the target PEEP set at 20 cmH_2_O and the target Ppeak set at 40 cmH_2_O. Individualized PEEP will be obtained by Cstat titration in obese patients. The effect of iPEEP on perioperative oxygenation index, lung collapse area, and incidence of PPCs in obese patients will be observed. At the same time, through detection of inflammatory factors in perioperative period, we tried to explore the mechanism of iPEEP on lung-protective function in obese patients.

In conclusion, this study tried to verify the following hypotheses: individualized PEEP titrated by Cstat combined with other lung-protective strategies will improve oxygenation and decrease atelectasis in obese patients during laparoscopic surgery. This study will provide a simple and feasible individualized PEEP titration method in obese patients. The result will provide direct clinical evidence for the next step to further refine the specific implementation of lung protection strategies in obese patients and add them to the link of surgical ERAS in obese patients.

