## Background

It is quite certain that postoperative pulmonary complications (PPCs) result in more morbidity and mortality, as well as prolong hospital stays. According to the type of surgery and the definition of PPCs, the incidence of PPCs has been reported to range from 5 to 33% [1, 2]. Considering that approximately 234 million patients worldwide require surgical treatment under general anesthesia each year [3], reducing the incidence of PPCs may have a great impact on global mobility and mortality. In recent years, more and more attention is paid to intraoperative mechanical ventilation strategies, which may affect PPCs in addition to the preoperative optimization of patients’ status and operation style.

Recently, an international expert consensus recommendation about lung-protective ventilation for the surgical patient was reported [4]. In the expert consensus, the following was strongly recommended: preoperative pulmonary risk evaluation, an individualized mechanical ventilation which include a tidal volume (*V*_*T*_) of 6–8 ml/kg predicted body weight (PBW), positive end-expiratory pressure (PEEP) of 5 cmH_2_O, and alveolar recruitment maneuvers (RM). Among these lung-protective ventilation strategies, individualized PEEP is important to prevent processive alveolar collapse. RM can reverse alveolar collapse but have limited benefit without sufficient PEEP. However, how to set individualized PEEP remains a matter of debate.

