This trial will verify the following hypothesis: individualized PEEP titrated by the best static lung compliance (Cstat), combined with other lung-protective ventilation strategies, compared with the conventional setting of PEEP, can reduce atelectasis and PPCs in obese patients at intermediate to severe risk for PPCs. Through evaluation of atelectasis and ventilation distribution by electrical impedance tomography (EIT) of obese patients before and after laparoscopic surgery, we confirm the effect of iPEEP on oxygenation and postoperative PPCs in obese patients. Meanwhile, we observe the changes of perioperative pulmonary inflammatory factors and other health indicators (length of stay, hospital costs), so as to confirm its effectiveness and significance of iPEEP in reducing postoperative pulmonary complications in obese patients.

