### Sample size calculations

The primary outcome measures of this study were oxygenation index (PaO_2_/FiO_2_) and the ratio of lung collapse area to normal lung tissue by preoperative and postoperative EIT. According to the literature report [10], the ratio of pulmonary collapse detected by EIT in obese patients with individualized peep (iPEEP) set by EIT compared with PEEP 5 cmH_2_O was 6.2 ± 4.1% vs. 10.8 ± 7.1%, with a significant difference (*P* = 0.017). We hypothesize that the Cstat-titrated iPEEP will improve the rate of postoperative lung collapse in obese patients, with a probability of *α* = 0.05 to allow for type 1 error, *β* = 0.1 to allow type 2 error, and power 0.90; according to the mean of two groups obtained in the literature, 35 cases are needed for each group by using the PASS 20.0 software. A final sample size of 40 per group accounts for a 10% dropout rate in case follow-up.

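### The Discussion claims adequate power for four outcomes, but only EIT lung collapse was sized; for PPCs the claim fails over much of the cited incidence range, and for oxygenation and inflammatory factors it has no stated basis

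*Protocol article*

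**What the plan says.** The first paragraph of the Discussion says "This study is adequately powered to test the hypothesis that an individualized PEEP titrated by Cstat ventilation strategy can benefit obese patients" and lists the outcomes covered: "in terms of perioperative oxygenation index, proportion of collapsed lung area, change in inflammatory factors, and incidence of PCCs" ("PCCs" is evidently a misprint for PPCs). The sentence carries no qualification.

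The section on sample size calculations names oxygenation index and EIT lung collapse as primary outcomes but uses figures for collapse only: 6.2 ± 4.1% with individualized PEEP against 10.8 ± 7.1% with PEEP 5 cmH2O, with "0.05 to allow for type 1 error" and "to allow type 2 error, and power 0.90". It concludes that "according to the mean of two groups obtained in the literature, 35 cases are needed for each group", raised to 40 per group for 10% dropout. It gives no effect size, SD or event rate for oxygenation index, inflammatory factors or PPCs.

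The section on study endpoints lists inflammatory factors and PPCs as secondary. The Background says "the incidence of PPCs has been reported to range from 5 to 33" per cent, depending on the type of surgery and the definition, and its hypothesis is that the strategy "can reduce atelectasis and PPCs in obese patients at intermediate to severe risk for PPCs". The Discussion also cites atelectasis in up to 45% of obese patients after upper abdominal surgery. The statistical analysis section plans Fisher's exact test at P < 0.05 for proportions, with a risk ratio and 95% CI.

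**The concern.** This is a positive statement that goes beyond the calculation behind it; the point does not rest on something the article has left out. One continuous outcome was sized, and the power was then claimed for three more, one of which is a binary endpoint that may be uncommon.

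PPCs matter most here. They are the patient-relevant outcome, and they appear in the hypothesis in the Background. If the trial is described as adequately powered for them and the comparison is not significant, a reader is entitled to take that as evidence that the strategy does not reduce PPCs. A trial of 80 patients cannot support that inference unless the base rate is high and the effect very large.

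**Working it through.** **1. Reproduce the stated sample size (EIT collapse).** Inputs from the sample size section: difference 10.8 − 6.2 = 4.6 points; SDs 4.1 and 7.1; α = 0.05; power 0.90; 1:1 allocation. Sidedness is not stated.

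- Root-mean-square SD = √[(4.1² + 7.1²)/2] = √33.61 = 5.80.
- At 35 per group, SE = √[(4.1² + 7.1²)/35] = √(67.22/35) = 1.386, so the noncentrality is 4.6/1.386 = 3.32 on 68 degrees of freedom.
- Two-sided power from the noncentral t is 0.897 at 34 and 0.905 at 35 per group (Welch 0.903 at 35). The required number is therefore 35, as stated. A one-sided test would need 28, so the plan's figure is two-sided.
- Dropout: 35/0.9 = 38.9, or 39. The stated 40 is within rounding and fits 20 blocks of four. Power at a full 40 per group is 0.94.

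The calculation is sound for EIT collapse.

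**2. Power for PPCs.** Inputs: 40 per group (before dropout) and Fisher's exact test, two-sided, P < 0.05. The article fixes neither a control rate nor an effect, so both are assumptions. The control rates span the Background range of 5–33%, with 45% (the atelectasis figure) added as a generous case. Power is the sum over all pairs (x₁, x₂) with Fisher P < 0.05 of Bin(x₁; 40, p₁) × Bin(x₂; 40, p₂).

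| Control | iPEEP | Assumed change | Power |
|---|---|---|---|
| 45% | 22.5% | halved | 0.48 |
| 33% | 16.5% | halved | 0.32 |
| 33% | 18.9% | same ratio as EIT, 6.2/10.8 | 0.22 |
| 20% | 10% | halved | 0.16 |
| 10% | 5% | halved | 0.04 |
| 5% | 2.5% | halved | 0.005 |
| 33% | 11% | cut by two thirds | 0.59 |
| 45% | 15% | cut by two thirds | 0.79 |
| 33% | 5% | cut by 85% | 0.89 |
| 33% | 4% | cut by 88% | 0.92 |

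At 35 per group, 33% against 16.5% gives 0.27. The normal approximation at 40 per group gives 0.40 for the same rates.

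**3. The low end, with the largest possible effect.** Suppose the iPEEP group has no PPCs at all. Five control events against none gives Fisher P = 0.055; six against none gives P = 0.026. Significance therefore needs at least six control events in 40, and power is P(X ≥ 6), X ~ Bin(40, p₁):

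- 5% control rate: 0.014
- 10%: 0.206
- 15%: 0.57

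In this part of the cited range no effect of any size is adequately powered.

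**4. Size needed for a halving from 33%.** n per group = [1.960·√(2p̄(1−p̄)) + z·√(p₁(1−p₁) + p₂(1−p₂))]²/(p₁−p₂)², with p̄ = 0.2475.

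- 80% power: (1.960 × 0.6103 + 0.8416 × 0.5991)²/0.165² = 106.2, so 107 per group.
- 90% power: (1.960 × 0.6103 + 1.2816 × 0.5991)²/0.165² = 141.7, so 142 per group.

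**5. Oxygenation index and inflammatory factors.** No difference or SD is stated for any of them, so no power can be computed from the article.

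**The case against.** The PPC figures rest on assumptions that the article does not make. The 5–33% range is general, across surgery types and definitions. This trial enrols patients with BMI ≥ 32.5 and ARISCAT ≥ 26, and its PPC endpoint is positive if any one of twelve conditions occurs, so the control rate could be above 33%. The sentence is also Discussion prose that changes no endpoint, test or sample size, and the sample size section shows openly which outcome drove the number.

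Much of this stands. A reader might infer from the 32% figure that PPC power is at most about one third. The documents do not support that as a bound: it needs a control rate no higher than 33%, a reduction no greater than one half, and Fisher's test. A two-thirds reduction from 33% gives 0.59, and a fall to 5% gives 0.89. The 45% figure is not a fixed control rate either: it is stated as an upper value for atelectasis alone.

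A reader might also conclude that oxygenation index and the markers are underpowered. That too is unsupported: their power is unknown.

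Finally, it is tempting to ask for PPCs to be taken out of the Background hypothesis. That would be a preference. PPCs are already secondary, nothing labels them confirmatory, and the closing hypothesis of the Discussion names only oxygenation and atelectasis.

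What the objection does not rescue is the sentence itself. Nothing in the article supports adequate power for three of the four outcomes, and for PPCs the claim fails outright in the lower part of the cited range whatever the effect.

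**Conclusion.** The concern holds in this form: the Discussion claims adequate power for four outcomes on the strength of a calculation for one. The EIT calculation is correct.

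For PPCs, adequate power would require both a base rate near or above the top of the cited range and a very large effect; from 33%, 90% power is reached only with a reduction of roughly 85% or more. These results assume 40 analysed per group and Fisher's test at two-sided 0.05; the control rates and reductions are illustrative. For oxygenation index, a named primary endpoint, and for inflammatory factors, the claim is unsupported and cannot be checked. It is a defect of wording with consequences for interpretation; the design itself is unaffected.

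**What to change.** Rewrite the opening sentence of the Discussion so that:

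- the 90% power claim applies only to the difference in EIT collapse proportion;
- oxygenation index, inflammatory factors and PPC incidence are described as not formally powered. For oxygenation index the alternative is to add a calculation with a stated difference and SD, which is preferable because it is a primary endpoint;
- PPCs are reported as a secondary estimate, using the risk ratio and 95% CI already planned, with a note that a non-significant result is not evidence of no benefit.

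The Background hypothesis can stay as it is. The cost is a few lines of text and a less favourable claim; the sample size, endpoints and tests do not change.

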## Trial status

The first participant was enrolled on November 3, 2019, and the first version was developed on June 26, 2019, the protocol version is the first version and the No is V1.0/2019.06.26. The recruitment will be completed on December 31, 2020. To date, 36 participants have been recruited. This trial is still ongoing.

## Data Availability

After the study is completed, the data will be open to the public through the Research Manager (ResMan) platform (http://www.medresman.org/login.aspx) within 6 months.

## Abbreviations

PPCs: Postoperative pulmonary complications
iPEEP: Individualized positive end-expiratory pressure
Cstat: Static lung compliance
FiO_2_: Inspiratory fraction of inspired oxygen
EIT: Electrical impedance tomography
PBW: Predicted body weight
RM: Recruitment maneuvers
*V*_*T*_: Tidal volume
CRF: Case report forms
ARISCAT: The Assess Respiratory Risk in Surgical Patients in Catalonia
BMI: Body mass index
COPD: Chronic obstructive pulmonary disease
VAS: Visual analogue scale
PSC-VC: Pressure-control-volume compensation mode
Pplat: Plateau airway pressure
Ppeak: Peak airway pressure
1:E: Ratio between inspiratory and expiratory time
PaO_2_: Partial pressure of arterial oxygen
PCT: Procalcitonin
